## Dosage and Dosing Schedule

***Dihydroartemisinin (DHA, 20/40 mg) and Piperaquine (PPQ, 160/320 mg) = Artekin (Sigma-Tau)***

Medications will be administered as close as possible at the following times:

Day 0: hour “X”

Day 1: hour “X” + 24 hours

Day 2: hour “X” + 48 hours

The number of tablets will be based on bodyweight (see the relevant table in Appendix II).

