# PATIENT WITHDRAWAL CRITERIA

During the study, the following conditions are reasons **for stopping the study treatment and/or for excluding the patients from further efficacy assessments:**

1. Any treatment failure (including early failures);

2. Withdrawal of informed consent;

3. Use of antimalarial drugs (or antibiotics with antimalarial activity) outside of the study protocol;

4. Persistent vomiting of study drugs **on Day 0**  (at least twice the same dose);

5. Failure to complete the study treatment

6. Investigator's request for safety reasons (for example, onset of serious adverse events, necessitating study interruption);

6. Lost to follow-up (unable to locate the patient) before Day 28.

Patients with one or more of the conditions listed above will have to be followed-up for the safety assessment until Day 42

These reasons for premature withdrawing will be referred to Day 28 (primary evaluation time).

The reasons for withdrawing between Day 29 and Day 42 will also be recorded in the study CRF.

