# PROTOCOL VIOLATIONS

A protocol violation occurs when an event happens that does not allow for accurate interpretation of response to treatment.

Patients meeting one of the following criteria will be considered protocol violations but will not be withdrawn from follow-up:

- **violation of any eligibility criteria;**
- PCR unclassifiable results;
- failure to attend a follow-up visit on Days 0-2 and patient cannot be located within 6 hours of scheduled time;
- failure to attend two consecutive follow-up visits from Day 3 to Day 28 (visits from Day 3 to 28 must take place within 24 hours of the scheduled time).

**The violations listed above are not valid reasons for withdrawing the patients from follow-up (both efficacy and safety assessments). On the contrary, the Investigator must do his/her best to respect the allowed time windows at every visit, even if a violation occurred at a previous visit (i.e. a previous visit did not take place or occurred outside the allowed time window).**

**The protocol violations listed above will not be taken into account for establishing patient inclusion in the Intention-To-Treat population while they will be a reason for excluding the patients from the Evaluable population**.

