## Population Analysed

The following populations will be considered for the statistical analysis of efficacy.

**Intention-to-Treat (ITT) Population**. Defined as all randomized patients who will take at least one dose of the study treatment. All patients who withdrew from the study for one of the reasons listed in section 5 as well as the patients for whom the PCR is not interpretable or missing will be evaluated as failures. For the robustness analyses, these patients will be evaluated in different ways in this population (see section 9.2).

**Modified Intention-to-Treat (modified ITT) Population**. Defined as the ITT population with the exclusion of the lost-to-follow-up patients before Day 28 for unknown reasons (non informative drop-outs). More specifically, patients withdrawing from the study for reason 7 (see section 5) will be excluded, while all other withdrawals will be counted as failures (these reasons might be potentially considered correlated with lack of efficacy, i.e. are referred to as informative drop-outs). The patients for whom the PCR is not interpretable or missing will be assigned the result “recrudescence” or “re-infection” according to the ratio between these outcomes which was observed among the evaluable PCRs within each treatment group. This rule about PCR will be applied for the primary analysis. For all analyses for which the knowledge of the outcome is needed for each patient individually (for example, the Breslow Day test or the logistic regression or the analyses where a baseline covariate is needed), different scenarios will be considered, i.e. the most two extreme ones of considering all patients with not interpretable or missing PCRs as failures or as successes and the intermediate one of excluding them all.

**Per-Protocol (PP) Population**: defined as all randomized patients who will be eligible according to the study protocol, will receive at least 80% of the study medication, will have the Day 28 assessment, will not take other anti-malarial drugs and, in case of the presence of asexual parasite stages on thick or thin blood smears, will have an evaluable PCR. The protocol violations listed below will also be considered reasons for excluding the patients from this population:

 failure to attend a follow-up visit on Days 0-2 and patient cannot be located within 6 hours of scheduled time;

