 failure to attend two consecutive follow-up visits from Day 3 to Day 28 (visits from Day 3 to 28 must take place within 24 hours of the scheduled time and from Days 14 to 28 within 48 hours of the scheduled time).

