# Study Committees

## Steering Committee

The Steering Committee (SC) comprises at least one investigator from each participating region and will assess the progress of the trial. The members of the SC will address policy and operational issues related to the protocol. The SC has responsibility for protecting the scientific conduct and integrity of the trial. Its functions include:

- Review of the protocol before ethic committee approval,
- Formulation of recommendation for any change in the design and operations of the trial during the course of the trial, when needed,
- Exclusion of patients from the per protocol analysis.

The members of the Steering Committee will be specified in the Terms of Agreement document that will be prepared no later than the first face-to-face meeting of this Committee

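### Entry to the co-primary per-protocol population rests on two conflicting visit windows, a dose rule that treats one missed dose differently by arm, and exclusions with no stated masking

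*Combined protocol and SAP*

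**What the plan says.** Section 9.2.1 requires the lower confidence limit to exceed -0.05 in each of the modified ITT and PP populations, so PP is co-primary.

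- **Visit window.** A child leaves PP after failing to attend two consecutive visits between Day 3 and Day 28. Section 9.1 adds that these visits "must take place within 24 hours of the scheduled time and from Days 14 to 28 within 48 hours". Section 6 has the same criterion with one limit: "visits from Day 3 to 28 must take place within 24 hours of the scheduled time". For its listed violations section 6 says "they will be a reason for excluding the patients from the Evaluable population", a population that section 9.1 does not define.
- **Dose rule.** Section 9.1 admits to PP a child who "will receive at least 80% of the study medication". Section 3.13 schedules three DHA+PPQ doses, the last at "Day 2: hour “X” + 48 hours", and six Coartem doses, at hours 0, 8, 24, 36, 48 and 60.
- **Incomplete treatment.** Reason 5 in section 5 is "Failure to complete the study treatment". The section's lead-in makes each listed reason grounds for stopping treatment, for leaving further efficacy assessment, or both. Section 9.1 counts every withdrawal except loss to follow-up as a failure in the modified ITT.
- **Who decides.** Section 15.1 lists among the committee's functions "Exclusion of patients from the per protocol analysis". On its make-up it says: "The Steering Committee (SC) comprises at least one investigator from each participating region". Section 3.1 describes the trial as open label.

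**The concern.** A co-primary population should be fixed by rules that give one answer per child, mean the same in both arms, and cannot be applied with the result in view. On the text as it stands, two programmers could build different PP sets from the visit rule. The dose rule tolerates one whole missed dose in the reference arm and none in the test arm. If children who miss a dose are cured less often, keeping them only in the Coartem arm lowers its PP cure rate and raises the test-minus-reference difference. That makes it easier to exceed -0.05. Finally, nothing says that those who rule on exclusions are kept from treatment or outcome, or that they finish before the database is locked.

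**Working it through.** **Visit window.** Take a child seen 30 hours off schedule on both Day 21 and Day 28, and suppose that an out-of-window visit counts as not attended (the plan does not say).

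| Text applied | Limit on Days 21 and 28 | Result |
|---|---|---|
| Section 9.1, first clause | 24 h | two consecutive failures, out of PP |
| Section 9.1, second clause | 48 h | both attended, in PP |
| Section 6 | 24 h | out of the Evaluable population |

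The conflict therefore reaches only children with two failed visits in a row, at least one of which fails solely by being 24 to 48 hours off schedule on Day 14, 21 or 28. To see the scale, assume that each of these three visits is 24 to 48 hours off schedule with independent probability p. The chance of a consecutive pair (14 and 21, or 21 and 28) is p² + p² - p³ = 2p² - p³:

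- p = 0.05: 0.0050 - 0.0001 = 0.5%
- p = 0.10: 0.020 - 0.001 = 1.9%
- p = 0.20: 0.080 - 0.008 = 7.2%

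The documents give no value for p. Pairs that involve a late Day 7 visit or a wholly missed visit would add to these figures.

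**Dose rule.** Share received = doses received / doses scheduled, compared with 0.80.

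- Coartem, one dose missed: 5/6 = 83.3%, passes. Two missed: 4/6 = 66.7%, fails.
- DHA+PPQ, one dose missed: 2/3 = 66.7%, fails.
- DHA+PPQ, half a dose lost: 2.5/3 = 83.3%, passes.

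In whole doses, the minimum for PP is 5 of 6 in one arm and 3 of 3 in the other.

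**Direction and size.** Let x be the share of Coartem PP children who are one dose short, q their cure rate, and 93% the PP cure rate expected in section 3.4.1. Keeping them lowers the Coartem PP rate by x(0.93 - q). The documents supply neither x nor q. On assumed values:

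- x = 2%, q = 85%: 0.02 × 0.08 = 0.16 points
- x = 5%, q = 70%: 0.05 × 0.23 = 1.15 points
- x = 10%, q = 50%: 0.10 × 0.43 = 4.3 points

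The results run from negligible to most of the 5-point margin, so this is not an estimate. The direction is towards non-inferiority whenever q is below 93%.

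**Section 5 against section 9.1, for a Coartem child with 5 of 6 doses.**

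- Reason 5 applied, with the child removed from efficacy assessment: a failure in the modified ITT and, without the Day 28 assessment, outside PP. The allowance disappears.
- Reason 5 applied as stopping treatment only: a failure in the modified ITT, yet evaluable in PP.
- Reason 5 not applied to one missed dose: evaluable in both.

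The text permits all three.

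**Exclusion decisions.** Masking is stated for PCR reading (sections 3.1 and 3.8) and for the Data Monitoring Board's review of part of the primary efficacy data (section 15.2). Section 15.1 states none for PP exclusions. As a sensitivity only, take 700 DHA+PPQ children in PP (70% of 1000) with 7% failing, which is 49. Removing 5 failures gives 1 - 44/695 = 93.67%, a rise of 0.67 points; removing 10 gives 1 - 39/690 = 94.35%, a rise of 1.35 points. The number removed is assumed, and nothing suggests that it would happen.

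**The case against.** The strongest reply is that the practical effect may be very small.

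- All doses are given under observation, night doses to outpatients are supervised at home, and spare tablets are packed for re-dosing (sections 3.6, 3.12 and 3.14).
- A child who misses a Day 0 to 2 visit and is not located within 6 hours already leaves PP in either arm, which removes some children with a missed dose.
- Non-inferiority must also pass in the modified ITT, so a shift in PP alone cannot produce the claim.

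All of this stands. It limits the likely size, but it does not give the two arms the same rule.

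A reader might infer three stronger points that the documents do not support:

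- *That the 80% rule purifies only the test arm.* The rule refers to medication, not doses, and a DHA+PPQ child with 2.5 of 3 doses passes. The asymmetry holds for whole missed doses only, and reason 5 may remove it.
- *That unmasked investigators decide PP membership.* Section 15.1 says that the committee includes investigators, not that it consists of them. Full membership is left to a Terms of Agreement document. No section says that members see allocation or outcome when they decide. What can be said is that no masking is stated.
- *That the tighter window erodes PP power.* Exclusion needs two consecutive failed visits, and the plan does not say that a late visit is a failed one. The 30% PP attrition in section 3.4.1 already covers protocol violations, and nothing shows which window it assumed. No loss of power can be tied to the window.

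**Conclusion.** The point holds as a set of conflicts and gaps in the definition of a co-primary population.

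- The two windows for Days 14 to 28, and the two population names, are contradictions in the text. Their reach is limited to children with consecutive failed visits of the kind described, and depends on a late visit counting as not attended.
- The difference in the dose rule is exact for one whole missed dose: 83.3% kept against 66.7% dropped. It leans towards non-inferiority if missed doses reduce cure. Its size cannot be estimated from the documents and may be small with observed dosing. Sections 5 and 9.1 must be reconciled before anyone can say whether the allowance exists at all.
- For exclusions, the gap is the absence of stated masking and timing in an open-label trial. It is not evidence that decisions would be biased.

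The stated power figures are not in question here. The changes are worth making because they are cheap and remove discretion from a population that must pass for the claim to be made.

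**What to change.** 1. In section 9.1, state one window for each visit, and say whether an out-of-window visit counts as not attended. Use the same text and the same population name in section 6.
2. Reconcile the PP adherence criterion with reason 5 in section 5, so that one missed dose has the same consequence for the PP analysis in both arms. One way is to require all scheduled doses for PP, counting successful re-doses. This concerns membership of the analysis population only; how section 5 is to be read for stopping treatment is for the sponsor to settle.
3. Apply the PP criteria by program. Have any judgement cases decided before database lock, on listings that show neither treatment nor outcome. Masking the review already assigned in section 15.1 is enough. The Data Monitoring Board's blind review covers a percentage of the primary efficacy data, so its remit should not be assumed to include PP membership.

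The cost is wording in sections 5, 6, 9.1 and 15.1, plus one masked listing. If the all-doses criterion is chosen, a few Coartem children with 5 of 6 doses may leave PP.

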## Efficacy

9.2.1 Analysis for showing non-inferiority of Artekin vs Coartem

The primary analysis will be based on a 97.5% (one-sided) Confidence Interval (CI) computed on the difference between the 28-day PCR corrected cure rates of the test and the reference treatments, respectively.

In order to claim that Artekin is non-inferior to Coartem the lower limit of the CI must be > -0.05 in both the modified ITT and the Per Protocol populations. The analysis on the more pure ITT population (see section 9.1) will be used for investigating robustness of results (see below).

The method for computing the CI will be specified in the SAP.

For computing the PCR-corrected cure rate, the patients who are diagnosed to be re-infected will be counted as successes (they have to be terminated on that day of follow-up) while the patients for whom the PCR is not interpretable or the sample is unavailable will be treated differently depending on the population considered (see section 9.1).

9.2.2 Historical comparisons

In order to compare the study results with the historical ones, the criteria described in the WHO document (“Assessment and Monitoring of Antimalarial Drug Efficacy for the Treatment of Uncomplicated Falciparum Malaria – 2003”. See chapter 7, section 7.3) will be used. Therefore, the failure rates will be estimated through survival analysis (Kaplan-Meier method) in each treatment group individually considered. This analysis will be carried-out in the per-protocol population and the results obtained in each of the two treatment groups will be judged against the threshold of 90% (there is consensus among the malaria experts in recognising that the threshold of 90% should be considered as a “rule of thumb” for judging efficacy)..

Robust analysis will be performed on the more pure ITT population by applying the following methods:

1. All patients who withdrew from the study for one of the reasons listed above (from 1 to **7**) will be evaluated as failures.

2. Patients who withdrew from the study for reasons that cannot be considered uncorrelated with the study treatments (i.e. reasons from 1 to **6**) will be counted as failures (i.e. assigned with a 0 value), while the patients prematurely interrupting the study for reason **7** will be assigned with a value ranging from 0.5 to 0.9 (imputation of a postulated probability of success for the patients for whom the treatment outcome could not be evaluated). Finally, all cured patients will be assigned with a 1 and this transformed endpoint will be summarized in terms of means and corresponding standard errors by treatment group.

3. The analysis of the 28-day PCR corrected cure rates will be performed by means of the survival analysis techniques, where the non informative lost-to-follow-up patients (i.e. patients withdrawing for unknown reasons) will be censored at the time of exiting the study.

The impact of these strategies on the conclusions will be carefully evaluated and discussed

The Breslow Day test or logistic regression will be used to evaluate homogeneity across centers. In this respect, each center would need to have at least two failures for each treatment in order for large sample chi-square approximations to be applicable. If this type of condition does not apply, exact logistic regression will be used to address homogeneity across centers. In addition, if the sample sizes are sufficiently large within centers so that each treatment has at least five failures within each center, a confidence interval adjusted for centers as strata will be computed (see Koch and others, Statistics in Medicine, 1998).

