## Sample Size

3.4.1 Sample size computation

The study is designed as a non-inferiority trial.

The level of the PCR-corrected cure rate at day 28 for Arthemeter+Lumefantrine has been estimated, through a literature search, to be in the range 90%-92%32-33 in the Intention-To-Treat (ITT) population. The opinion of physicians and experts in malaria treatment has been sought for defining the non-inferiority margin, and this has been set at 5%.

An unequal randomization with 2:1 structure was chosen because it assures a larger sample size for the DHA+PPQ group which provides the following advantages:

- a more precise estimate of the DHA+PPQ cure rate;
- a bigger sample for the integrated safety data base of DHA+PPQ, that renders more likely the elucidation of rare adverse reactions, if any.

From an ethical point of view, this choice appears reasonable in view of the previous data on DHA+PPQ, in terms of both safety and efficacy.

Sample size was initially (see original version of the protocol) computed considering the original formulation of the primary objective, which required the use of a simulation (details are provided in a separate document - see Sample Size and Design Justification for The Pivotal Clinical Trials of Dihydroartemisinin+ Piperaquine**)**.

Having divided the two criteria of non-inferiority and comparison of study results with historical ones, power has been recomputed for each of the two objectives as described below**.**

For the non-inferiority analysis, the clinical and statistical specifications for the sample size computations are as follows:

- Primary endpoint = PCR-corrected cure rate at day 28.
- Primary analysis = based on 97.5% one-sided confidence intervals for the difference in cure rates.
- Alpha = 0.025 (one-sided).
- Power = 80%.
- Cure rate of Coartem in the pure ITT population = at least 91%.
- Non-inferiority margin for the difference (test-reference) = -0.05.
- Randomization: based on a 2 :1 allocation scheme (test : reference).
- Rate of patient attrition in the modified intention-to-treat population as compared to the pure ITT population (i.e. rate of non-informative withdrawals) = 10%. Expected 28-day PCR corrected cure rate in this population = 91%.
- Rate of patient attrition in the Per Protocol Population as compared to the ITT population (i.e. rate of withdrawals for any reason and protocol violations) = 30%. Expected 28-day PCR corrected cure rate in this population = 93%.

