- Primary Analysis Populations = both the modified Intention To Treat (ITT) and the Per Protocol Populations.

With these assumptions, the sample size of 1500 patients (1000 in the Artekin group and 500 in the Coartem group) provides a power of approximately 83% for the lower bound of a 97.5 one-sided confidence interval for the treatment difference being above –0.05 in the modified ITT and 82% for the same analysis in the Per Protocol population (for the power calculation both continuity correction and inequality of variances under the null hypotheses have been considered).

For the historical comparisons, the clinical and statistical specifications for the sample size computations are as follows:

- Anticipated population proportion of clinical failures = as high as 10%.
- Confidence level = 95% (two-sided interval).
- Precision = 5 percentage points.
- Rate of patient attrition in the Per Protocol Population as compared to the ITT population (i.e. rate of withdrawals for any reason and protocol violations) = 30%.

According to Annex 4 of the WHO document “Assessment and Monitoring of Antimalarial Drug Efficacy for the Treatment of Uncomplicated Falciparum Malaria – 2003”, a sample size of at least 200 patients would be required in each treatment group for estimating the proportion of clinical failures to within a 5 percentage point of the true value with 95% confidence.

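### The planned robustness analyses include no scenario in which lost DHA+PPQ children do worse than lost Coartem children, and method 2 with one common value is a weak check on the modified ITT result

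*Combined protocol and SAP*

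**What the plan says.** Section 9.2.1 allows the non-inferiority claim only if the lower confidence limit exceeds -0.05 in both the modified ITT and the Per Protocol populations. Section 9.1 removes from the modified ITT the children lost before Day 28 for unknown reasons, treating that loss as non-informative. The Per Protocol population requires a Day 28 assessment, so it drops them too. Section 3.4.1 sets the "Rate of patient attrition in the modified intention-to-treat population as compared to the pure ITT population" at 10% and does not split it by arm.

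The pure ITT analysis "will be used for investigating robustness of results (see below"). The methods it points to are listed under section 9.2.2:

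- Method 1: every withdrawal, including loss to follow-up, is a failure.
- Method 2: other withdrawals score 0, cured children score 1, and a lost child "will be assigned with a value ranging from 0.5 to 0.9 (imputation of a postulated probability of success"). The output is a mean and a standard error for each arm.
- Method 3: survival analysis with lost children censored.

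Method 2 does not say whether both arms share one value. No between-arm interval, margin test or rule for discordant results is attached to any of the three. (The reason 7 cited there is the second item numbered 6 in section 5.)

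**The concern.** Both deciding analyses rest on the same untestable assumption: that a lost child would have fared like the observed children in the same arm. The trial is open label, so loss related to treatment is possible. The harmful case for a non-inferiority claim is that lost DHA+PPQ children do worse than lost Coartem children. A robustness analysis should show how much worse they could do before the conclusion fails.

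None of the three methods specifies that case. Methods 1 and 3 apply one rule to both arms. Method 2, on its simplest reading, gives both arms the same number. That pulls the arms together, which is cautious in a superiority trial and lenient in a non-inferiority trial. If method 2 passes more readily than the modified ITT, its agreement with the modified ITT says little.

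**Working it through.** **Inputs (section 3.4.1).** "Non-inferiority margin for the difference (test-reference) = -0.05"; "Alpha = 0.025 (one-sided"); "Randomization: based on a 2 :1 allocation scheme (test : reference"); "the sample size of 1500 patients (1000 in the Artekin group and 500 in the Coartem group"); for the modified ITT, "Expected 28-day PCR corrected cure rate in this population = 91"%, used here for both arms; 10% loss. Assumptions added here: equal loss by arm, Wald limits (section 9.2.1 leaves the interval method to the SAP), and method 2 held to the same -0.05 margin.

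**Reproducing the stated power.** Power = Φ((0.05 − cc)/SE − 1.96), with cc = (1/nT + 1/nC)/2.

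- Modified ITT, 900/450 at 91%: SE = √(0.91×0.09×(1/900+1/450)) = 0.0165; cc = 0.0017; power 83.3% (plan: about 83%).
- Per Protocol, 700/350 at 93%: SE = 0.0167; cc = 0.0021; power 81.7% (plan: 82%).

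Without the continuity correction, the modified ITT figure is Φ(0.05/0.0165 − 1.96) = 85.7%. The comparisons below are all made without it.

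**Methods 1 and 2 as a score on 1000/500.** With loss l, cure rate p among observed children and value v for lost children:

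- arm mean m = (1−l)p + l·v
- variance s² = (1−l)p + l·v² − m²
- difference at l = 0.1: d = 0.9(pT − pC) + 0.1(vT − vC)
- pass rate = Φ((d + 0.05)/SE − 1.96), with SE = √(sT²/1000 + sC²/500)

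A common v removes the second term of d, so a true -0.050 becomes -0.045.

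Example, v = 0.9 at equality: m = 0.819 + 0.090 = 0.909; s² = 0.819 + 0.081 − 0.8263 = 0.0737; SE = √(0.0737×0.003) = 0.0149; pass rate Φ(3.36 − 1.96) = 92.0%. At 86% against 91%: d = −0.045, SE = 0.0160, pass rate Φ(0.31 − 1.96) = 5.0%.

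| Analysis | Pass rate at true -0.05 (86% v 91%) | Pass rate at equality (91%) | SE at equality |
|---|---|---|---|
| Modified ITT | 2.5% | 85.7% | 0.0165 |
| Method 1 (v = 0) | 4.2% | 66.0% | 0.0211 |
| Method 2, v = 0.5 | 4.7% | 86.5% | 0.0163 |
| Method 2, v = 0.7 | 4.9% | 90.6% | 0.0153 |
| Method 2, v = 0.9 | 5.0% | 92.0% | 0.0149 |

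If 20% were lost in each arm (assumption), method 2 would pass 8.3% to 9.7% at a true -0.05.

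**Simulation.** In 400,000 trials of the same design, the pass rates at a true -0.05 were 2.2% (modified ITT) and 4.4% to 4.5% (method 2). In 4,000 trials with failures and losses spread over follow-up, they were 1.7% and 3.2% to 3.5%. Method 3 kept the mean difference at -0.050 and passed 2.1% at a true -0.05 and 87.4% at equality. The levels vary with the model; the ordering of method 2 above the modified ITT does not.

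**Standard error.** A fixed v treats the lost child's outcome as known. Were it a 0/1 draw with probability v, the variance would be m(1−m): at v = 0.5, SE = √(0.869×0.131×0.003) = 0.0185 rather than 0.0163; at v = 0.9, 0.0158 rather than 0.0149.

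**Different values by arm, true equality at 91%.**

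- 0.7 (DHA+PPQ) v 0.9 (Coartem): d = 0.1×(−0.2) = −0.020, SE 0.0150, pass rate Φ(0.030/0.0150 − 1.96) = 52%.
- 0.5 v 0.9: d = −0.040, SE 0.0154, pass rate Φ(0.010/0.0154 − 1.96) = 9.5%.

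Put as a tipping point: if both arms were observed at exactly 91%, 0.7 v 0.9 puts the lower limit at −0.020 − 1.96×0.0150 = −0.0494, just inside the margin. With 0.6 v 0.9 it is −0.030 − 1.96×0.0152 = −0.0597, outside.

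**Unequal loss (assumption: 12% DHA+PPQ, 6% Coartem), true equality.** With a common v, d = 0.06(v − 0.91): −0.055 for method 1, −0.025 for v = 0.5, −0.001 for v = 0.9. Reversing the imbalance (8% v 14%) reverses the sign.

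**The case against.** The strongest reply has four parts, and most of it stands.

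- A reader might infer that these analyses make non-inferiority easier to declare. They do not: section 9.2.1 rests the claim on the modified ITT and Per Protocol alone, and section 9.2.2 sets no margin test for method 2. The pass rates above apply a test that the plan does not state.
- A reader might infer that all three methods are lenient. Method 3 imputes nothing and does not dilute. Method 1 is more lenient at a true -0.05, but stricter than the modified ITT once the true difference is better than about -0.035, and it passes only 66% at equality.
- A reader might infer that the plan forbids values that differ by arm. It is silent: 0.5 against 0.9 lies inside its own range, and the SAP could settle the matter.
- A reader might infer that any true difference shrinks. That needs similar loss by arm. With unequal loss, methods 1 and 2 can create a difference in either direction, so they do respond to differential loss.

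What the reply does not supply is the missing scenario. Responding to different loss rates is not the same as examining different outcomes among the lost. Method 3 assumes again that loss is non-informative. Silence on the arms leaves the choice open until results may be known.

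**Conclusion.** The point holds in a limited form. Children lost before Day 28 are absent from both deciding analyses, and no specified robustness scenario makes lost DHA+PPQ children worse off than lost Coartem children. Method 2, read as one common value with about 10% loss in each arm, would pass roughly twice as often as the modified ITT at a true -0.05 and slightly to moderately more often at equality. It is therefore a weak check on that result. An arm-specific choice within the plan's own range moves the difference by up to 4 points against a 5-point margin.

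This rests on equal loss, Wald limits, a common value (a reading of silent text) and a margin test added for comparison. It does not show an inflated type I error or a defect in the primary analysis. It is a shortcoming of a supportive analysis, worth correcting before unblinded results are seen.

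**What to change.** Amend method 2 in the SAP as follows:

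- Vary the value for lost children separately by arm over a two-way grid across 0.5 to 0.9, including combinations unfavourable to DHA+PPQ.
- For each cell, report a confidence interval for the difference whose variance reflects the imputation, in place of arm means with standard errors alone.
- Show where the lower limit crosses -0.05, and state how a discordant result will bear on the conclusion.
- Keep methods 1 and 3, and say explicitly that all three serve section 9.2.1.

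Imputing under the non-inferiority null (lost Coartem children at the observed Coartem rate, lost DHA+PPQ children at that rate minus 0.05, by multiple imputation) is an optional addition. It is not free: in simulation it passed about 81% of trials at equality, against about 87% for the modified ITT. That price falls on a sensitivity analysis only. Otherwise the cost is SAP wording and a little programming on data already collected; primary power is unaffected.
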